Eligible study participants will need to meet the following criteria: patients (1) aged 20 years or older with (2) an LVEF below 40% or a structural heart disease confirmed via cardiac imaging, (3) an implantable cardioverter–defibrillator (ICD) or a cardiac resynchronisation therapy (CRT) device compatible with Biotronik Ltd. (Berlin, Germany) wireless monitoring devices, and (4) a predicted life expectancy of more than 6 months, (5) capable of understanding and completing the simple consent form, and (6) never having been enrolled in clinical trials that involve RM before. Patients will be informed that if they want to withdraw their consent to this study, they can stop participating in this clinical trial, and their data will be collected until the withdrawal date. Exclusion criteria are as follows: (1) patients with a life expectancy of 6 months or less, (2) patients with cognitive impairment who are unable to understand the information regarding wireless monitoring or who are unable to provide consent, and (3) patients currently participating in another clinical trial that may be affected by the implementation of wireless monitoring. Patients who have previously participated in clinical trials, those who are currently participating in a clinical trial that the investigator judges will not affect or be affected by this trial, and those who are participating in other observational studies are eligible for this study. If the patient wishes to discontinue participation in the study or dies within 6 months of participation (to be noted separately), they will be considered withdrawn from the study.

Informed consent will be obtained from each participant included in the study. Details of the study protocol are available at ClinicalTrials.gov (study ID: NCT05971225). Patient enrolment started in November 2023 at two centres (40 and 10 patients were enrolled in St. Vincent’s Hospital and Eunpyeong St. Mary’s Hospital, respectively, as of 1 August 2024) after Institutional Review Board approval (VC23DIDI0148; approval date: 11 July 2023) and will continue until October 2025. Follow-up data will be acquired for 24 months after enrolment. We plan to collect the final data in December 2027, and the results of the ReVe study will be published in 2028.

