### 2.2. Data Collection

The baseline data include patient demographic details, such as gender, date of birth, cardiac device type, implantation date, and indication for the device implantation. They also include health conditions (such as a history of hypertension or heart failure) and information on prescription drugs at enrolment, obtained from electronic medical records.

We determined that a historical group is necessary to compare and analyse patients’ hospitalisation rates and satisfaction before and after the application of RM. Patients in the historical group were diagnosed with heart diseases a considerable time before enrolment. They will be compared to patients in the initiating group to determine whether the hospitalisation rate improves with the application of RM.

The two patient groups in this study are as follows: (1) the historical group consisting of patients who already have CIEDs (implanted after January 2020) and have attended outpatient device check-ups (225 patients planned); (2) the initiating group consisting of patients who will undergo CIED implantation after providing informed consent for participation in this study (225 patients planned). We want to investigate the convenience of and satisfaction with RM applications for patients who have yet to experience RM and obtain information on major adverse cardiac and cerebrovascular events (MACCEs) that occurred before RM was applied. Considering the patients’ average lifespan, analysing MACCEs only in the historical group will cause limitations in the future. Therefore, we will also determine the MACCEs in the initiating group for comparison. After informed consent was provided, the patients or their caregivers received a CardioMessenger Smart transmitter (CM) paired with their CIED. The CM collects information through wireless technology (including therapeutic interventions, arrhythmic events, thoracic impedance information, lead data, and device-related alerts), encodes the collected biometric data, and transmits it to a medical institution. Daily RM will be initiated the day after device pairing. In the case of long business trips or other types of extended travelling, patients are asked to take the CM with them and keep it connected to a charger at night near their bedside.

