### 2.3. Statistical Analysis

We will compare outcomes before and after RM via paired *t*-tests in the historical group. We will compare the clinical-, RM-, and device-related variables via independent samples *t*-test between the historic and initiating RM groups. Tests for normality will be provided. If data is non-normal, then *t*-tests and means/standard deviations should be avoided, and Mann–Whitney/Wilcoxon and medians/interquartile ranges should be preferred. For the *t*-tests, we will reject the null hypothesis when the two-sided *p*-value is less than 5%. For the analysis of patient baseline data, continuous variables will be presented as means and standard deviations and analysed using *t*-tests or Wilcoxon rank-sum tests. Categorical variables will be presented as frequencies and percentages. For the analysis of satisfaction with the survey, paired *t*-tests (parametric test) or Wilcoxon signed-rank tests (non-parametric test) will be performed. For surveys conducted only after monitoring, ordinal variables will be analysed using the Mann–Whitney U test, and continuous variables will be analysed using chi-square tests. For patients not completing the follow-up, censoring will be based on the last data collected. Cumulative event probabilities will be estimated with adverse health outcomes, such as patient deaths, inpatient admissions, and MACCEs. Hazard ratios and 95% confidence intervals will be generated with Cox proportional hazards models. For subgroup analyses, the interaction term between the prespecified groups, based on the type of underlying heart disease and LVEF, will be evaluated for the primary outcome. Because of the interim analyses, we will adopt the O’Brien–Fleming method for statistical corrections. For all analyses, we will use two statistical software packages: Stata, version 18 (StataCorp LLC, College Station, TX, USA), and R, version 4.05 (R Foundation for Statistical Computing, Vienna, Austria).

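### The paired before/after comparison in the historical group is not limited to non-fatal events, although no death can occur there before remote monitoring starts

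*Protocol article*

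**What the plan says.** All references are to the protocol article.

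- **Who is in the group.** Section 2.2 defines "the historical group consisting of patients who already have CIEDs (implanted after January 2020) and have attended outpatient device check-ups". Section 2.1 adds that "Informed consent will be obtained from each participant included in the study" and requires "a predicted life expectancy of more than 6 months".
- **When RM begins.** After consent the patient receives the transmitter, and "Daily RM will be initiated the day after device pairing" (section 2.2).
- **What the before/after comparison is for.** Section 2.2 says that "a historical group is necessary to compare and analyse patients’ hospitalisation rates and satisfaction before and after the application of RM". The same section also wants to "obtain information on major adverse cardiac and cerebrovascular events (MACCEs) that occurred before RM was applied".
- **How it is tested.** Section 2.3: "We will compare outcomes before and after RM via paired" *t*-tests in the historical group, with rank-based tests if the data are not normal. It does not list the outcomes.
- **What MACCE contains.** The abstract names cardiovascular death among the primary outcomes. The list of study aims in section 2.2 includes cardiac mortality under MACCE, and the primary endpoint in that section combines cardiovascular death with admissions for existing cardiovascular disease.
- **Early deaths.** Section 2.1 treats a patient who dies in the first 6 months of participation as withdrawn, with the death noted separately.

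**The concern.** The before and after periods do not admit the same events. A historical patient who died between implantation and enrolment could not consent and is not in the data, so before RM only non-fatal events can be observed. After RM, both non-fatal events and deaths can be. A paired test of a MACCE outcome that includes death would set admissions and other non-fatal events on one side against those events plus deaths on the other. Whatever RM does, the death component can only count against it.

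Two things are at stake. A real reduction in admissions could be partly hidden. And the comparison could be read as bearing on mortality, the question with which the abstract opens, although it cannot inform that question in either direction.

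**Working it through.** **1. Can a death occur before RM?** Consent comes from each participant (2.1), and RM starts after consent and pairing (2.2). The period before RM therefore lies wholly before a date that each patient had to reach alive. The number of deaths in it is zero by design, whatever the true death rate.

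**2. Does adding the initiating group help?** No. Those patients consent before implantation and then receive RM, so they supply no deaths before RM either.

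**3. The plan's own event rate.** Section 2.1 assumes a 2-year MACCE incidence of 10% to 15%, with a 5% margin at 95% confidence. With n = 1.96² × p(1 − p)/0.05²:
- p = 0.10: 3.8416 × 0.09/0.0025 = 138.3, so 139.
- p = 0.15: 3.8416 × 0.1275/0.0025 = 195.9, so 196.

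Both match the stated 139 to 196 per group, so 10–15% is used below.

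**4. Illustration with no RM effect.** Assumptions not in the document: constant hazards, equal 24-month windows, and a share s of first MACCEs that are cardiovascular deaths.
- Total cumulative hazard: H = −ln(1 − p).
- Before RM (non-fatal events only): 1 − exp(−H(1 − s)).
- After RM: p.
- After RM with deaths in months 0–6 dropped: c = s(1 − exp(−H/4)), and the risk is (p − c)/(1 − c).

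Example, p = 0.10 and s = 0.20: H = 0.1054. Before: 1 − exp(−0.0843) = 8.08%. Ratio: 10.0/8.08 = 1.237. With early deaths dropped, c = 0.20 × 0.0260 = 0.0052, after = 0.0948/0.9948 = 9.53%, and the ratio is 1.179.

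| 2-year MACCE | s | Before | After | Ratio | After, early deaths dropped | Ratio |
|---|---|---|---|---|---|---|
| 10% | 10% | 9.05% | 10.0% | 1.105 | 9.77% | 1.079 |
| 10% | 20% | 8.08% | 10.0% | 1.237 | 9.53% | 1.179 |
| 10% | 30% | 7.11% | 10.0% | 1.407 | 9.29% | 1.307 |
| 15% | 10% | 13.61% | 15.0% | 1.102 | 14.66% | 1.077 |
| 15% | 20% | 12.19% | 15.0% | 1.230 | 14.32% | 1.174 |
| 15% | 30% | 10.75% | 15.0% | 1.395 | 13.97% | 1.299 |

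**5. Effect on the paired test.** Simulated paired *t*-tests (225 patients, 20,000 runs, two-sided 5%, before and after independent within a patient, early deaths not dropped) falsely found harm in 10.4% (p = 10%) and 13.9% (p = 15%) of trials at s = 20%, and in 19.3% and 26.5% at s = 30%. The nominal rate in that direction is 2.5%. False benefit was at most about 0.4%.

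**6. Sensitivity to the look-back window.** With a window of T months, the risk before RM is 1 − exp(−H(1 − s)T/24). It equals the 24-month risk after RM when T = 24/(1 − s), that is 26.7, 30.0 and 34.3 months for s = 10%, 20% and 30%. Beyond that the sign of an unadjusted yes/no comparison reverses. At p = 0.10, s = 0.20 and T = 48, the risk before is 1 − exp(−0.1686) = 15.5%, against 10.0% after. Implantation after January 2020 and enrolment up to October 2025 allow windows of up to about 70 months.

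**The case against.** The strongest reply is that the criticised analysis is inferred. No sentence says that a composite including death will be paired before and after RM. Section 2.2 gives hospitalisation and satisfaction as the purpose of that comparison, and both are non-fatal. It words the primary endpoint as MACCE after RM and brings in the initiating group for comparing MACCEs, conceding that MACCE analysis in the historical group alone is limited. Section 2.3 assigns deaths, admissions and MACCEs to cumulative event probabilities and Cox models. The choice of outcomes for the paired test could also sit in a fuller document that is not shown.

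Much of this stands: a reader might infer that the plan expressly commits to a paired MACCE test, and it does not. But the article does plan to collect MACCEs from before RM, and section 2.3 leaves the paired outcomes unrestricted, so following the text as written permits the faulty comparison. The concession in section 2.2 rests on patients' lifespan, not on the condition of having survived to enrolment.

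A reader might also infer that the comparison must show a net rise in MACCE after RM. The document does not support that. The look-back is unstated and the sign can reverse with a long one, as shown. Events clustered around diagnosis or implantation would favour RM, and the 6-month rule removes some deaths after RM. An offsetting bias of unknown size does not make the comparison valid, however.

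Finally, larger error rates can be produced, for example about 61% false harm with 10% admissions and 8% deaths. That implies a composite of 1 − 0.90 × 0.92 = 17.2%, outside the plan's 10–15%, so it is not relied on here.

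**Conclusion.** The flaw in the death component holds and follows from the design: no death can be observed before RM, so a paired MACCE outcome that includes death is biased against RM in that component. The claim is conditional on section 2.3 being applied to MACCE, and it does not extend to the net direction of the whole comparison.

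The size is illustrative only, since the document gives neither a death share nor a look-back window. Under the assumptions above, with shares of 10–30%, the spurious ratio is about 1.1 to 1.4, or about 1.08 to 1.3 with early deaths dropped. False harm of about 10–27% applies to shares of 20–30% before early deaths are dropped; it would be lower with them dropped. This calls for a cheap clarification before the before/after analysis is run, and does not undermine the study as a whole.

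**What to change.** In section 2.3, state that:

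1. the before/after analysis in the historical group uses only non-fatal events that can occur in both periods, namely cardiovascular admissions, as the purpose in section 2.2 already implies;
2. these are expressed as rates per person-time over a stated window before RM;
3. death and death-inclusive MACCE are reported only from enrolment onwards, as cumulative incidence, with no before/after test;
4. this comparison gives no evidence on an effect of RM on mortality.

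Removing death alone is not enough. Deaths after RM shorten the time at risk for admission and would lower admission counts in RM's favour, and an unstated window leaves even the sign of a crude comparison open. Under the illustration's assumptions the restricted rate ratio is expected to be about 1.0 when RM has no effect. The change does not remove any clustering of events around implantation, which is a further reason to state the window.

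The cost is a few sentences, plus the person-time in each period, which follows from dates. The downside is that the paired analysis no longer covers the full MACCE composite, which it could not validly do.

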In this study, we may also use the successor model of the CM family. The package provided to participants will consist of the CM and a power supply module. The CM receives information from the paired CIED once daily, typically at night. The transmitter is used for communication with the CIED, and the data received from the device are encrypted and sent to the company website (www.biotronik-homemonitoring.com/, accessed on 6 February 2025) via the data module. Healthcare providers receive an alert from the website when the device detects a change in the patient’s heart rhythm, identifies issues with the device itself, or prompts a reminder for periodic, overall CIED check-ups.

The ReVe study will be the first prospective multicentre study in South Korea in which the following conditions are fulfilled:(1)Collecting data from all visits or admissions during the study period, classified as device-related, patient cardiovascular condition-related, or non-cardiovascular condition-related events. These visits will also be categorised as either physician-driven (RM-based) or patient-driven hospital visits.(2)Analysing MACCEs, such as myocardial infarctions/cerebrovascular accidents, thromboembolic events, exacerbation of heart failure, admissions due to cardiac causes, cardiac-related mortality (as a proportion of overall mortality), and other cardiac events.(3)Collecting and analysing data on RM variables weekly, including thoracic impedance and lead sensing, to elucidate their correlation with disease progression, admission, and mortality.(4)Evaluating the staffing/time requirements for RM using electronic medical records (log-in and log-out times are recorded).(5)Analysing and comparing patient satisfaction questionnaires after RM every 6 months (Table 1) via telephone or during office visits (between the historical and initiating groups). The questionnaire evaluates the efficacy of RM and the perceived quality of care due to RM. It contains nine questions with five answer categories each (strongly agree, agree, neutral, disagree, and strongly disagree).

Questions (1) to (3) contain the primary outcomes, and (4) and (5) include the secondary outcomes. These are summarised in Figure 1.

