Patients with CIEDs, except those on warfarin or those with other relevant medical issues (followed up on other clinic consultation schedules), are scheduled for routine clinical follow-ups every 3–6 months. Patient satisfaction surveys are scheduled every 6 months to assess changes in satisfaction levels over time and explore varying trends across device types (‘Survey on telehealth patient experience’ by [name], 2023 [15], modified Korean version 1.3; Table 1). The study is summarised in Figure 1, and the process of the study is also available in Supplementary Table S1.

The primary endpoint will be any MACCE after RM (cardiovascular-related death and hospital admissions related to pre-existing cardiovascular disease), defining variables that are predictive of MACCE and unexpected hospital visits during RM. The secondary endpoints will be patient satisfaction with the time, cost, and quality of care after adopting RM (determined via questionnaires on a 6-month basis) and the staffing/time requirements during RM (measured using electronic medical records).

All files and data generated during the study are stored in a safety deposit box or as copied files secured with passwords accessible only to the investigators. Because this study includes personal identifiers and sensitive information, the data will not be openly accessible. Anonymised study data will be made available to researchers upon reasonable request after the study results are published.

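### The admission part of the primary endpoint is not limited to unplanned admissions, so elective cardiac stays meet the MACCE rule and device-related stays may

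*Protocol article*

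**What the plan says.** All of the relevant endpoint text is in section 2.2 (Data Collection) of the protocol article.

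- **Definition.** "The primary endpoint will be any MACCE after RM", which is then spelled out as "cardiovascular-related death and hospital admissions related to pre-existing cardiovascular disease". The only test for an admission is its relation to the existing heart disease.
- **Event list, item (2).** Among the MACCEs to be analysed are "exacerbation of heart failure, admissions due to cardiac causes, cardiac-related mortality (as a proportion of overall mortality), and other cardiac events". This carries no restriction to unplanned stays either.
- **First classification, item (1).** All visits and admissions are "classified as device-related, patient cardiovascular condition-related, or non-cardiovascular condition-related events".
- **Second classification, item (1).** "These visits will also be categorised as either physician-driven (RM-based) or patient-driven hospital visits".
- **Link to the endpoint.** The section adds that items (1) to (3) hold the primary outcomes.
- **Where the plan does separate expected from unexpected.** The sentence defining the endpoint goes on to "defining variables that are predictive of MACCE and unexpected hospital visits during RM". The qualifier is attached to visits, not to the admissions inside MACCE.

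The historical group is "patients who already have CIEDs (implanted after January 2020) and have attended outpatient device check-ups". Section 2.2 gives the purpose of the comparison as finding out whether hospitalisation improves once RM is applied.

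**The concern.** A MACCE endpoint is meant to capture major adverse events. Consider three admissions: (a) decompensated heart failure, (b) elective generator replacement or upgrade, and (c) scheduled angiography or ablation for the known disease. The first is plainly an adverse outcome. The third meets the written rule just as well, and the second may.

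This matters because admissions are central to the study's question. RM is expected to act through earlier detection of deterioration and has no obvious route to preventing elective stays. Adding them to both sides of a comparison pulls the ratio towards one. If the Cox models are fitted to the first event, an elective stay would also take the place of a later genuine event in the same patient.

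**Working it through.** **1. Does the wording let elective stays in?**

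| Text in section 2.2 | (a) decompensation | (b) elective device replacement | (c) scheduled angiography or ablation |
|---|---|---|---|
| Endpoint definition | meets it | open | meets it |
| Item (2), cardiac admissions | meets it | open | meets it |
| Item (1), three classes | cardiovascular | most naturally device-related | cardiovascular |
| Item (1), physician- or patient-driven | either | does not settle it | does not settle it |

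Column (c) meets the rule at every step. Column (b) stays open: the device-related class exists, but no sentence removes it from MACCE.

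**2. The plan's own figure.** Section 2.1 assumes a two-year MACCE rate of 10-15%, with 95% confidence and a 5-point margin. Using n = 1.96² × p(1−p) / 0.05²:

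- p = 0.10: 138.3, rounded up to 139
- p = 0.15: 195.9, rounded up to 196

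Both match the stated 139 to 196 per group. For the total, 2 × 196 = 392 and 392/0.9 = 436. The plan states 442, which is close but not exact, and nothing here depends on the difference.

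**3. Effect on the counted rate.** The documents give no elective-admission rate. Assume a proportion q of 2%, 5% or 10% over two years, independent of true events. Counted rate = 1 − (1−p)(1−q).

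| True rate p | q = 2% | q = 5% | q = 10% |
|---|---|---|---|
| 10% | 1 − 0.90 × 0.98 = 11.8% | 1 − 0.90 × 0.95 = 14.5% | 1 − 0.90 × 0.90 = 19.0% |
| 15% | 1 − 0.85 × 0.98 = 16.7% | 1 − 0.85 × 0.95 = 19.3% | 1 − 0.85 × 0.90 = 23.5% |

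**4. Dilution of a contrast.** Take the two ends of the plan's range as an illustrative contrast, 10% against 15%. The true risk ratio is 0.10/0.15 = 0.67. With the same q on both sides:

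- q = 2%: 11.8/16.7 = 0.71
- q = 5%: 14.5/19.25 = 0.75
- q = 10%: 19.0/23.5 = 0.81

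**5. Effect on precision.** With 10% loss, 225 × 0.9 gives about 202 evaluable patients per group. Half-width = 1.96 × √(p(1−p)/202). It is 4.9 points at 15%, 5.4 points at 19.0% and 5.9 points at 23.5%. The 5-point target would be missed, but only modestly.

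**The case against.** The strongest reply is that this argues from silence. The article never says that planned admissions count, it condenses a fuller protocol, and event-level rules are commonly kept there. Part of this stands: it is right to say that planned admissions are *not excluded*, and wrong to say that the plan expressly *includes* them. But the article does not simply omit the rule. It states one for the primary endpoint, and that rule is too wide as stated.

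Three stronger readings are tempting, and the documents do not support them.

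- **Device replacements score as MACCE.** Item (1) classes device-related admissions apart from cardiovascular ones, and the endpoint wording sits closer to the latter. Replacements may count; it is not established that they do.
- **The historical group is biased upwards.** Its devices date from January 2020 onwards, so a reader might expect more replacements. If an extra 5% fell wholly in one group, the hazard ratio under equal true risk would be ln(0.90 × 0.95)/ln(0.90) = 1.49, or ln(0.85 × 0.95)/ln(0.85) = 1.32. This needs the whole excess in one group and none in the other. The documents give no device longevity, and the argument leans on replacements, whose status is itself open.
- **The planned rate of 10-15% is thereby exceeded.** The event definition behind that figure is not shown. It may already include elective stays.

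Section 2.3 also does not say that the Cox models use the first event or that such an event ends follow-up, so that harm is conditional.

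One objection changes the remedy. An admission may be scheduled because RM showed an arrhythmia or deterioration. It is planned, yet it reflects disease and is a consequence of RM. A bare restriction to unplanned stays would drop such admissions and could flatter RM. This stands.

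**Conclusion.** The point holds as a defect of wording in the primary endpoint. Elective cardiac admissions meet the rule as written, and device-related admissions may. The direction of the effect on a comparison is dilution when elective stays are spread evenly.

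The size cannot be derived from the documents. Under the assumed 2-10% elective rate, independent of true events, a true 10% would read 11.8-19.0% and a true 15% would read 16.7-23.5%. These figures show sensitivity to the assumption and are not an estimate for this study. Imbalance between groups is a possibility only.

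The definition should be corrected before outcome data are analysed at the first interim analysis. It does not undermine the sample-size arithmetic, whose per-group range reproduces.

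**What to change.** - **Endpoint sentence.** Limit the admission component to unplanned admissions for a cardiovascular cause. Keep any admission prompted by an RM alert or by clinical worsening, even if it was scheduled.
- **Identifying those admissions.** The physician-driven (RM-based) category already collected can mark the RM-prompted ones, provided that it is recorded for admissions as well as visits. Worsening found in another way needs its own reason code. Apply the same rule to the period before RM, when no RM alert could exist, so that the two periods are counted alike.
- **Device-related class.** State that elective device-related admissions are outside MACCE.
- **Admission record.** Add a planned/unplanned flag.
- **Reporting.** Report planned admissions separately, and give the all-admission version of the endpoint as a sensitivity analysis.
- **Planning assumption.** State which definition the 10-15% rate refers to, so that it and the endpoint agree.

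The cost is a lower event count and a small classification burden. All admissions are already collected under item (1). The flag would have to be completed retrospectively for patients already enrolled (40 + 10 = 50 at two centres as of 1 August 2024) and for admissions before RM in the historical group.
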